### 2.7. Outcomes of Interest

#### 2.7.1. Primary Outcome

The primary outcome will be identifying changes in body weight from baseline to 1 and 6 months and between groups. To measure body weight and BMI, we will use TANITA MC-780MAS Segmental. In the welcome session, participants will be presented with the primary outcome, which is maintaining a healthy weight or losing 5% if overweight.

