## Abstract

Aim: to analyze the efficacy of an educational online intervention focused on lifestyle changes in reducing body weight from baseline to 6 months in the pre-diabetic population of 18–45 years old in Extremadura (Spain). Methods: a single-blind, multicenter randomized parallel-comparison trial with two intervention groups in a 1:1 ratio will be carried out. Participants will be randomly assigned to intervention A or B with 37 cases in each group according to inclusion criteria of being enrolled or working at Extremadura University, scoring >7 points on the Findrisc test and not having diagnosed diabetes mellitus or physical disabilities. Intervention-A group will have access to online information about healthy diet and exercise. Intervention-B group will have access to a six-session educational program regarding behavioral changes in diet and exercise habits. They will complete follow-up activities and have a personal trainer and motivation. The primary outcome will be identifying changes in body weight from baseline to 1 and 6 months and between groups. The secondary outcomes will be accomplishing regular physical activity (>30 min/day or >4 h/week), decreasing sugary food intake or avoiding it altogether, increasing vegetable/fruit intake and lowering HbA1c levels to non-diabetic status when necessary.

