The study hypothesis is that online educational intervention focused on lifestyle changes is effective in reducing body weight when engaging activities are encouraged and present throughout the first weeks of behavioral modifications.

The aim of the study is to analyze the efficacy of an online educational intervention focused on lifestyle changes in reducing body weight from baseline to 1 and 6 months in the pre-diabetic population of 18–45 years old in Extremadura (Spain).

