### 2.3. Sample Size

The primary outcome was body weight change at 1 and 6 months. The power calculation assumed a 14 kg SD in baseline weight and a 0.9 correlation between baseline and 6-month weight [31]. As such, a sample size of 74 (37 per group) was required to give the trial 80% power to detect a 4 kg difference in mean weight change between groups at 6 months (*p* < 0.05, two-sided test).

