## 3. Discussion

The striking increase in the incidence of type-2 diabetes mellitus and its broad consequences has led us to focus on preventing its development through educational interventions that reduce the associated risk regarding lifestyle choices [22,23,24,25].

However, studies in our target population are scarce mostly due to lower incidence compared with other age ranges. Notwithstanding that fact, given the chronic character that diabetes mellitus has, it is paramount to prevent its development at any age range. As a result, we chose to run a parallel-comparison trial so every patient—regardless of their allocation in the study—will be aware of their pre-diabetic status and make evidence-based and healthy changes in their lifestyle.

COVID-19 has strained and changed the healthcare system during these past two years, being a priority over chronic diseases [42]. Furthermore, both group and individual interventions onsite were suspended. However, telemedicine has increased and developed greatly, becoming an effective tool to deliver educational interventions. There have been research studies prior to and during COVID-19 that have proven the efficacy of online educational interventions [27,28,29]. As a result, these interventions have the potential to bridge the gap between the limited supply of healthcare resources and the growing demand for diabetes education.

There are several potential limitations of the planned study. First, the assessment of body weight changes from baseline to 6 months might reflect only those changes occurred in the short term. This will be taken into account in further research. Nonetheless, several studies have set up 6 months to collect endpoint assessments [28,31].

Second, even though all university staff will be included in the study, that is, low, middle and high educational status population, given the highest high-educational status population rate, the low and middle-educational status population might be underrepresented.

Third, by carrying out a parallel-comparison trial with two intervention groups, we expect changes in both groups. However, our study will assess whether follow-up and motivation are needed in achieving lifestyle changes, providing a viewpoint that could help healthcare professionals manage their workload more efficiently.

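### Weight change at 1 and at 6 months is jointly primary with no rule for which decides, while the abstract's aim and the power calculation rest on 6 months alone

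*Protocol article*

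**What the plan says.** The protocol article describes the primary outcome or aim in several places, and they do not agree.

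- **Abstract, aim:** efficacy "in reducing body weight from baseline to 6 months". The abstract's later outcome sentence adds 1 month.
- **Introduction, aim:** "reducing body weight from baseline to 1 and 6 months in the pre-diabetic population of 18–45 years old".
- **2.3 Sample Size, opening:** "The primary outcome was body weight change at 1 and 6 months".
- **2.3 Sample Size, calculation:** 37 per group for 80% power "to detect a 4 kg difference in mean weight change between groups at 6 months", two-sided at 0.05.
- **2.7.1 Primary Outcome, opening:** "The primary outcome will be identifying changes in body weight from baseline to 1 and 6 months and between groups".
- **2.7.1 Primary Outcome, closing:** in the welcome session "participants will be presented with the primary outcome, which is maintaining a healthy weight or losing 5% if overweight".
- **2.8.1 Statistical Analysis:** group differences in body weight will be examined and linear regression used for adjustment. No time point or primary contrast is named.

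**The concern.** A trial needs one stated comparison that decides whether it succeeded, and that comparison should be the one it was sized for. Here two time points share primary status without ranking, and only the later one has a power calculation.

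The practical risk is a split result. Section 2.6 puts all six sessions of intervention B within one month, so the 1-month visit falls close to the most intensive part of the programme. A difference at 1 month that has gone by 6 months could be reported as a positive primary result, and nothing in the text rules this out.

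Two further wordings widen the choice:

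- The phrase in 2.7.1 that joins change from baseline with change between groups can be read as making within-group change primary. Both arms receive an online intervention, and the Discussion says "we expect changes in both groups". A fall in weight within an arm could therefore appear even if B were no better than A, and it would not show efficacy.
- The goal given to participants is a yes/no result that depends on starting weight. A healthy-weight participant meets it with no change at all, which in a comparison of mean kilograms counts as no effect. It is not the same outcome as mean weight change, yet it carries the same label.

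**Working it through.** **Inputs from section 2.3:** SD of baseline weight 14 kg; correlation 0.9 between baseline and 6-month weight; difference 4 kg; two-sided alpha 0.05; power 80%; 37 per group.

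**1. Reproduce the stated sample size.**

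- Baseline-adjusted SD = 14 × √(1 − 0.9²) = 14 × √0.19 = 6.10 kg.
- n per group = 2 × (1.960 + 0.842)² × 6.10² / 4² = 36.5, rounded up to 37, total 74. This matches the plan exactly.
- Power at 37 per group: 4 / (6.10 × √(2/37)) = 2.82. This gives 80.5% by the normal approximation and 79.4% by the t distribution.
- For comparison, an unadjusted change score has SD 14 × √(2 × (1 − 0.9)) = 6.26 kg and needs 39 per group, total 78. This does not match.

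So the 74 belongs to one test: the baseline-adjusted difference between groups at 6 months, at two-sided 0.05.

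**2. Either time point is enough, each tested at 5%.** Under no effect at either time, familywise error = 1 − P(|Z₁| < 1.96 and |Z₂| < 1.96) for two correlated normal statistics. The documents give no correlation between the two test statistics, so a range is assumed.

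| Correlation | Familywise error |
|---|---|
| 0 | 9.75% |
| 0.3 | 9.5% |
| 0.5 | 9.1% |
| 0.7 | 8.3% |
| 0.8 | 7.8% |
| 0.9 | 7.0% |

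**3. Both time points are required.** Error does not exceed 5%. If the 4 kg effect and the 6.10 kg SD also hold at 1 month (an assumption), the power to succeed at both with 37 per group is 67%, 69%, 72% and 76% for correlations of 0.3, 0.5, 0.7 and 0.9 (normal approximation). All are below 80%.

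**4. Alpha split equally, 0.025 each.** Power at 6 months with 37 per group falls from 79.4% to 70.1% (t distribution), or from 80.5% to 71.8% (normal approximation). Restoring 80% would take 45 per group, total 90.

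**5. One primary test at 6 months.** Alpha stays at 5%, the total stays at 74, and power is as in step 1.

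**The case against.** Four points can fairly be made for the plan.

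- **A matching test exists.** A reader might infer that no test in the plan fits the power calculation. That is not so. Section 2.3 specifies the 6-month between-group difference, and the 74 reproduces for it. What remains is that 2.3 itself opens with both times as primary, and neither 2.7.1 nor 2.8.1 singles this contrast out.
- **Inflated error is not established.** A reader might infer that the trial will exceed 5%. That follows only if either time point is enough. The document states neither that rule nor the rule that both must succeed. A multiplicity rule may also sit in an analysis plan that is not shown. Such a plan could settle the rule, but it would not make the abstract, introduction, 2.3 and 2.7.1 agree.
- **The within-group reading is not the only one.** The sentence in 2.7.1 may simply mean change from baseline, compared between groups, as 2.3 puts it. For body weight, 2.8.1 mentions only differences between groups; its wording on change across visits concerns questionnaire scores. The Discussion lists expected change in both arms as a limitation, and the question it poses there, whether follow-up and motivation are needed, is one between the arms. No passage says that a within-arm fall would count as efficacy. This is an ambiguity to remove, not a planned false claim.
- **The goal may be motivational.** The closing sentence of 2.7.1 reports what participants are told. Section 2.8.1 gives no analysis of it and 2.3 no sample size, so the text does not support reading it as a competing efficacy endpoint. The label is still wrong.

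The timing argument has a limit too. The sessions fit within one month, but no end date is given for the personal trainer's follow-up, and contact remains available afterwards. It cannot be said that support stops at the 1-month visit.

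**Conclusion.** The concern holds as an inconsistency in the stated primary outcome. Two time points are jointly primary with no decision rule, while the abstract's aim and the only power calculation concern 6 months. The power calculation itself is sound for the contrast it describes.

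Each way of keeping both times primary has a cost: error above 5% under an either-time rule, or power below the stated 80% under a both-required rule or an equal split of alpha. The error figures rest on the assumed correlations. The both-required figures also assume the same effect and SD at 1 month. The loss from splitting alpha needs only the plan's own inputs and baseline adjustment.

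The within-group wording and the mislabelled goal are lesser faults of the same definition. The choice decides what counts as a positive trial, so it should be settled before outcome data are seen.

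**What to change.** State one primary outcome: the between-group difference (B minus A) in body weight at 6 months, adjusted for baseline weight, tested two-sided at 5%. Then:

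- make 1-month body weight a secondary outcome;
- report within-group changes descriptively;
- call the healthy-weight or 5% statement in 2.7.1 the participants' goal, not the primary outcome;
- use the same wording in the abstract (aim and outcome sentence), the introduction's aim, 2.3 and 2.7.1, and name the time point and contrast in 2.8.1.

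This is a change of wording. The sample size stays at 74 and every measurement is collected as planned. What is given up is a primary claim at 1 month.

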#### 2.7.2. Secondary Outcomes

All secondary outcomes will be assessed at baseline, 1 and 6 months after the intervention.

A secondary outcome will be accomplishing regular physical activity (>30 min/day or >4 h/week). To assess physical activity, participants will complete the RAPA questionnaire. This questionnaire in the Spanish version obtained good test–retest reliability (r = 0.906), a sensitivity of 76.6% and a specificity of 65.6% [36].

Another secondary outcome will be decreasing sugary food intake or avoiding it altogether and increasing vegetable/fruit intake. We will use the Tfeq-Sp, Yale food addiction and EEQ to assess current diet and willingness to change it. The Tfeq-Sp measures three concepts: cognitive restraint, emotional eating, and uncontrolled eating. These concepts are explained further in Jauregui-Lobera et al. [37]. The internal consistency of the Tfeq-Sp was determined by means of Cronbach’s α coefficient, with values ranging between 0.75 and 0.87 [37]. The Yale food addiction questionnaire identifies individuals with addictive behaviors toward food in accordance with substance dependence criteria. The validated Spanish version demonstrated internal consistency for the one single dimension solution of α = 0.95 [38]. The EEQ measures three factors: disinhibition, high-calorie food preference, and feelings of guilt. EEQ internal consistency was good (α = 0.753) [39].

Lowering HbA1c levels to non-diabetic status, when necessary, will also be a secondary outcome. To measure HbA1c, we will employ the Affinity A1c Analyzer.

Finally, changes in diabetes knowledge will be measured using the DKQ-24 questionnaire. This questionnaire was designed to assess overall diabetes knowledge according to content recommendations in the National Standards for Diabetes Patient Education Programs. The 24-item version of the DKQ-24 attained a reliability coefficient of 0.78, indicating internal consistency [40].

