### 2.2. Participants: Eligibility, Recruitment, and Allocation

Participants were eligible for this trial when in accordance with the following selection criteria:

As inclusion criteria: ages 18–45, FINDRISC screening result >7 points, being enrolled or working at the University of Extremadura. As exclusion criteria: HbA1c compatible with type 2 diabetes, diabetes diagnosis, mobility disability and/or comorbidities incompatible with moderate exercise. 

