### 2.8. Data Analysis

#### 2.8.1. Statistical Analysis

Descriptive statistics will be estimated for baseline patients and their characteristics. The similarity between groups at baseline will be calculated, followed by examining differences between groups in body weight. Covariates will be screened in bivariate analyses and included in multivariable analysis when related to outcomes *p* < 0.2. Covariates will include age, sex, center, BMI, HbA1c, lipid profile and blood pressure. Adjustment for confounding factors will be examined using linear regression. Questionnaire scores will be assessed, and changes will be sought between baseline, 1 and 6 months and between groups. All statistical analyses will be performed using IBM SPSS statistics version 27.0.

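### The physical-activity outcome is a yes/no status with two unequal thresholds and no account of baseline activity, while the analysis section describes changes in questionnaire scores

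*Protocol article*

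**What the plan says.** The abstract and section 2.7.2 of the protocol article both define this secondary outcome as a status reached. The abstract has "accomplishing regular physical activity (>30 min/day or >4 h/week" and section 2.7.2 has "A secondary outcome will be accomplishing regular physical activity (>30 min/day or >4 h/week". The instrument is named next: "To assess physical activity, participants will complete the RAPA questionnaire". The accuracy quoted for its Spanish version is "a sensitivity of 76.6% and a specificity of 65.6" (per cent); the cut-off and reference standard behind those figures are not given.

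On timing, section 2.7.2 says "All secondary outcomes will be assessed at baseline, 1 and 6 months after the intervention". Entry under section 2.2 requires "ages 18–45, FINDRISC screening result >7 points, being enrolled or working at the University of Extremadura", with no condition on current activity. The HbA1c outcome in section 2.7.2 is limited to participants who need the improvement; the activity outcome has no such limit.

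The only analysis text that covers RAPA is in section 2.8.1: "Questionnaire scores will be assessed, and changes will be sought between baseline, 1 and 6 months and between groups". The covariates listed there are demographic, centre, anthropometric, laboratory and blood-pressure variables. Baseline RAPA is not among them.

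**The concern.** Three features of the definition weaken the result it is meant to give.

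- **Unequal limbs.** The two amounts joined by the word or are not the same weekly total. Who qualifies depends on how the daily limb is read, and the article does not say.
- **No baseline.** A status at follow-up is not a change. A participant already above the threshold at entry can meet the outcome without altering anything, and such participants shrink the difference that the trial is looking for.
- **Outcome and analysis differ.** The outcome is attainment (yes/no) but the analysis describes score changes. Two endpoints are therefore open for one result, and the binary one loses information, perhaps a great deal given the accuracy that the article quotes.

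At stake is whether a real gain in activity in group B could be missed, and whether the reported activity result is the one that was specified.

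**Working it through.** **Plan's own figure.** Section 2.3 gives a sample size only for body weight; no power is stated for activity. It "assumed a 14 kg SD in baseline weight and a 0.9 correlation between baseline and 6-month weight", with a 4 kg difference, 80% power and two-sided 0.05. With baseline adjustment the variance is 14² × (1 − 0.9²) = 37.24 (SD 6.10). Then n = 2 × (1.960 + 0.842)² × 37.24 / 4² = 36.5, so 37 per group, as stated. Nothing below changes this figure; 37 per group is carried forward.

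**Thresholds** (abstract and 2.7.2).
- Daily limb: 30 min × 7 = 210 min = 3.5 h/week.
- Weekly limb: 4 h = 240 min, or 240 / 7 = 34.3 min/day. The gap is 30 min/week.
- Daily limb as an average: anyone above 240 min/week already averages more than 30 min/day, so the weekly limb is redundant.
- Daily limb as every day: 31 min on seven days is 217 min (3.6 h) and qualifies. Forty-five minutes on five days is 225 min (3.75 h) and fails both limbs. On the average reading the second person passes, since 225 / 7 = 32.1 min/day.

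**Baseline dilution.** Let b be the share already active who stay active, and d the difference in new attainment among the rest. The difference in status is (1 − b) × d. The article gives neither value, so both are assumptions. With d = 30 points:

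| b | Difference in status |
|---|---|
| 0% | 30 points |
| 10% | 27 points |
| 30% | 21 points |
| 50% | 15 points |

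**Misclassification of a binary RAPA result.** Inputs from 2.7.2: sensitivity 0.766, specificity 0.656. Assumptions: these apply to this cut-off, with equal error in both arms.
- Observed rate for true rate p: 0.766p + (1 − 0.656)(1 − p) = 0.344 + 0.422p.
- Share of a true difference observed: 0.766 + 0.656 − 1 = 0.422, so 57.8% is lost.
- If p = 0, 34.4% would still be classed as active.

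True rates below are assumed. Power is for two proportions, 37 per group, two-sided 0.05.

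| True rates | Observed rates | True difference | Observed difference | Power, true | Power, observed |
|---|---|---|---|---|---|
| 30% v 50% | 47.1% v 55.5% | 20 points | 8.4 points | 42% | 11% |
| 20% v 50% | 42.8% v 55.5% | 30 points | 12.7 points | 78% | 19% |
| 40% v 70% | 51.3% v 63.9% | 30 points | 12.7 points | 75% | 19% |

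**If error differs by arm.** Take true rates of 30% v 50% and lower the specificity in group B to 0.50 (assumed). Group B is observed at 0.5 × 0.766 + 0.5 × 0.50 = 63.3%. The difference is 63.3 − 47.1 = 16.2 points instead of 8.4.

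**The case against.** The other side has good points, and several stand.

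- **The rule can be applied.** Two limbs joined by the word or form a usable union, so there is no logical contradiction. That stands. A reader might infer that the rule definitely ranks less activity above more; this holds only if the daily limb means every day, which the article does not say. What remains is an ambiguous definition.
- **Baseline is measured and used.** RAPA is taken at baseline, and section 2.8.1 looks for change. A reader might infer that participants active at entry will be counted as successes. No section says so, and under randomisation they dilute the contrast without favouring an arm. How many active people enter is also unknown: the introduction lists physical activity among the FINDRISC items but gives no item points. The stated definition still leaves baseline out.
- **The accuracy figures may not transfer.** A reader might infer that RAPA removes more than half of any true difference. The documents do not support that. The 0.422 factor does not apply to a score analysis, and group B alone receives personal motivation (section 2.6), so its self-report error could differ.
- **False positives need not dominate.** In the 30% v 50% scenario they are 24.1 of 47.1 points (51%) at the lower rate and 17.2 of 55.5 (31%) at the higher. The share depends on rates that the article does not give.
- **Scores are already planned, and detail can sit elsewhere.** A journal article may leave the RAPA scoring rule to a fuller document, so its absence is not a finding. But the article itself names attainment as the outcome and then describes a different analysis; that mismatch is in the text.

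**Conclusion.** The point holds for a secondary outcome and is worth correcting. Three things follow from the text alone: the limbs are 3.5 and 4 h a week, the definition takes no account of baseline activity, and the stated outcome is not what section 2.8.1 analyses. The size of the effect is conditional. With a binary RAPA result, transferable accuracy figures and equal error in both arms, about 42% of a true difference in proportions would be observed. The dilution from already active participants depends on their share, which is unknown. Error that differs between arms could make the observed contrast larger than the equal-error calculation suggests, so the direction is not assured either. The primary outcome and the sample size are untouched.

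**What to change.** In sections 2.7.2 and 2.8.1, and in the abstract to match:

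1. Make the activity outcome the between-arm comparison of the 6-month RAPA score, adjusted for the baseline RAPA score. Six months is the time point to which the sample size refers.
2. Keep attainment as supportive only. Reconcile the two limbs into a single weekly threshold; which amount it should be is for the investigators to decide.
3. Report attainment among participants below that threshold at baseline.

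The cost is wording and a small change to the analysis, with no new data, since RAPA is already collected at baseline, 1 and 6 months. The downside is that a score difference is less intuitive than a percentage of responders, which is the reason to keep attainment alongside it. Moving to a score does not remove self-report error that differs between arms.

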### 2.4. Recruitment

All participants from 18 to 45 years old will be reached through a standardized email sent to their university’s account where they will find an explanation of the project and the informed consent form with the possibility of either accepting to participate or declining any participation. Five researchers will reinforce the alumni’s participation with a visit during class hours and welcome to the project and explain it further. In the case of the university’s workforce, these five researchers will contact them during work hours in their workplace.

After two weeks’ notice, all volunteers who had signed the informed consent form will be summoned to follow the screening path which will be carried out using the Spanish version of the FINDRISC, which is a validated eight-item European questionnaire related to diabetes risk factors. This questionnaire has been validated in Spanish by the Pizarra Study in a Spanish population aged 18 to 65 years old. The results showed a 22.2% positive predictive value and 96% negative [11]. The study DE-PLAN—also developed in Spain—showed a 75.9% sensitivity and 52.3% T2DM diagnosis specificity and 65.8% prediabetes diagnosis specificity [32,33]. Furthermore, its utility has been demonstrated all over the world [16,32,33,34,35].

The FINDRISC screening will be carried out by six research nurses at the university centers. To those eligible participants with Findrisc results >7 points, researchers will ask them whether they have any mobility disability and/or comorbidities incompatible with moderate exercise in order to exclude those participants who do not meet the inclusion/exclusion criteria.

All suitable participants will be informed about their prediabetes status. Consequently, they will be offered to enter the study and will be given information and the calendar for the study.

As a result of participating in the study, additional clinical data will be collected such as capillary blood samples to measure HbA1c and fasting plasma glucose, lipid profile, BMI and blood pressure.

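### The HbA1c secondary outcome conflicts with the HbA1c exclusion: read literally, every eligible participant already meets it at baseline

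*Protocol article*

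**What the plan says.** All references are to the protocol article.

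- **Outcome.** Section 2.7.2: "Lowering HbA1c levels to non-diabetic status, when necessary, will also be a secondary outcome". The abstract repeats it: "lowering HbA1c levels to non-diabetic status when necessary".
- **Timing.** Section 2.7.2: "All secondary outcomes will be assessed at baseline, 1 and 6 months after the intervention".
- **Eligibility.** Section 2.2: "As exclusion criteria: HbA1c compatible with type 2 diabetes, diabetes diagnosis". No numeric HbA1c cut-off is given. Entry requires a FINDRISC score above 7, not a raised HbA1c. The abstract's shorter list mentions only diagnosed diabetes and has no HbA1c exclusion.
- **Sequence.** Section 2.4 describes the FINDRISC screen, then a question about disability and comorbidities, then information about prediabetes status and the offer to enter. It continues: "As a result of participating in the study, additional clinical data will be collected such as capillary blood samples to measure HbA1c".
- **Analysis.** Section 2.8.1 lists HbA1c among the covariates. The comparisons it describes are of body weight and questionnaire scores.

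**The concern.** The outcome is a move into a state that the eligibility rule appears to require at entry. A responder outcome of this kind can be estimated only if some participants start outside the target state, and Section 2.2 removes the people who would do so on the ordinary meaning of non-diabetic.

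This is the only glycaemic outcome listed in a trial presented as diabetes prevention. Fasting plasma glucose is collected but is not named as an outcome. If the wording stays, the outcome will have to be dropped or reinterpreted at analysis. Choosing a threshold and a subset once results are visible would leave the HbA1c finding open to a charge of selective reporting.

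**Working it through.** **1. The plan's own figure.** The article gives no number for the HbA1c outcome. Its one calculation is for weight, in Section 2.3: "The power calculation assumed a 14 kg SD in baseline weight and a 0.9 correlation between baseline and 6-month weight". With a 4 kg difference, two-sided 5% and 80% power:

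- Baseline-adjusted SD = 14 × √(1 − 0.9²) = 6.10 kg.
- n per group = 2 × 6.10² × (1.96 + 0.84)² / 4², which rounds up to 37, or 74 in total. Power at 37 per group is 80.5%.

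The stated 74 is reproduced. It concerns weight only and neither supports nor weakens the HbA1c point.

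**2. Literal reading.** Let E be the people eligible under Section 2.2, and D those with diabetic-range HbA1c at baseline.

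- Section 2.2 excludes D, so E and D do not overlap.
- The outcome, as a change from baseline, needs a participant who starts in D and ends outside it.
- The number of eligible participants who can achieve it is therefore 0 in each group, and no between-group comparison can be estimated.

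A participant could enter the diabetic range at 1 month and leave it by 6 months, but that is not a lowering from baseline.

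**3. Loose reading.** Suppose non-diabetic means below the prediabetic range. The outcome can then occur in participants whose baseline HbA1c is in that range. The article does not give their number, and FINDRISC above 7 does not fix it, because the score is built from risk factors such as age, BMI, waist and family history. Purely as an assumption:

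| Assumed share in the prediabetic range | Of 74 | Per group of 37 |
|---|---|---|
| 10% | 0.10 × 74 = 7.4 | 3.7 |
| 50% | 0.50 × 74 = 37 | 18.5 |

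Even at the upper end, half of the randomised participants contribute nothing to the outcome.

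**4. Sequence and exclusions.** Three descriptions of the entry rule do not match:

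| Place | What it implies for diabetic-range HbA1c without a diagnosis |
|---|---|
| Section 2.2 | Not eligible |
| Abstract | Not mentioned; only diagnosed diabetes excludes |
| Section 2.4 | HbA1c is described after the offer to enter, so such a value could surface late |

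A person found late is still ineligible under Section 2.2, but ineligible is not the same as not enrolled. The text does not settle whether such people could be in the trial.

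**The case against.** The strongest reply is that the wording is loose rather than wrong. The population is called pre-diabetic throughout, participants are told of their prediabetes status, and the diabetic range is excluded. In that setting, the qualifier *when necessary* can be read as applying to people whose HbA1c is raised at baseline, with the target being a normal value. A missing cut-off is the kind of detail that an article may leave to a fuller document. HbA1c is also scheduled at every assessment, so no data are lost, and the primary outcome is untouched.

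Much of this stands. A reader might infer that 0 of the 74 enrolled participants can achieve the outcome, that it cannot occur at all, and that the trial will have no usable glycaemic result. The documents do not support that stronger reading, for three reasons:

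- The zero applies to eligible participants under the literal meaning. Section 2.4 and the abstract leave open that someone with an undiagnosed diabetic-range value is enrolled.
- Under the loose meaning, the relevant subset need not be empty.
- HbA1c is due to be measured at baseline, 1 and 6 months, so a usable comparison is available once the outcome is redefined.

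The reply does not remove the conflict. The article uses prediabetes as a term of its own, so *non-diabetic* does not naturally mean free of prediabetes, and nothing says that it does. The point is also not a complaint about omitted detail: an eligibility rule and an outcome are both stated, and they do not fit together. The loose reading restores the outcome only for a subset whose size the entry criterion does not control.

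**Conclusion.** The concern holds as a conflict between a stated outcome and a stated exclusion. On the literal reading, no eligible participant can achieve the HbA1c outcome relative to baseline. On the loose reading, only those with prediabetic-range HbA1c at entry can contribute: an unknown number, about 7 to 37 of 74 if the share is assumed to be 10% to 50%. That range is illustrative and has no source in the article. The description of when HbA1c is measured, and the abstract's narrower exclusion, are inconsistent with Section 2.2 and need reconciling.

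Severity is moderate. One of several secondary outcomes is affected; the primary weight outcome and its sample size of 74 are not. The conclusion rests on the article alone. A fuller protocol or analysis plan might define the term, but the published wording would still need correcting.

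**What to change.** 1. In the abstract and Section 2.7.2, define the outcome as the between-group difference in HbA1c at 6 months, adjusted for baseline HbA1c (ANCOVA), in all randomised participants with a measurement. Baseline HbA1c should be in this model by design, not subject to the p < 0.2 covariate screen in Section 2.8.1.
2. Optionally add, as a supporting outcome, the proportion moving from prediabetic to normal range among those in the prediabetic range at baseline, with the cut-off stated in advance and the denominator reported by group.
3. Reconcile the abstract, Section 2.2 and Section 2.4 on the HbA1c exclusion and on when HbA1c is measured relative to entry. Which entry rule applies is for the sponsor to decide.

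The cost is wording only. HbA1c is already scheduled at baseline, 1 and 6 months, so no visit, test or participant is added. The change should be dated and made before outcome data are examined by group.
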